### Outcome measures

#### Primary endpoint

To demonstrate the non-inferiority of immediate compared to early (within 24 h from the completion of surgery) removal of UC in patients undergoing MICR in terms of AUR. AUR is defined as the inability to urinate within 8 h after UC removal or difficulty of voiding with a postvoid residual volume (PVR) measured by ultrasound greater than 300mL.

#### Secondary outcome measure

To demonstrate the non-inferiority of immediate compared to 24-h removal of UC for the other short-term postoperative outcomes that could be influenced by the timing of UC removal:Rate of UTI defined by the presence of symptoms (dysuria, frequency, urgency, suprapubic pain, hematuria, or testicular pain) and positive urine culture. Urine culture is considered positive when yielding more than 10^5^ colony-forming units per ml.Rate of UC reinsertion considering all causes (e.g., AUR as well as need for redo surgery, need for ICU admission, etc.).Pain control until POD 3. Intensity of pain is evaluated according to the NRS score and measured at 6, 12, 24, 48, and 72 h from surgery.Return to bowel function. Return to bowel function is evaluated considering the time (days) needed for the bowel to open to gas and stool as well as for the patient to tolerate a liquid and solid diet.Return to passive and active mobilization. Mobilization is evaluated considering the time (days) needed for sitting on a chair and walking.Postoperative morbidity. Postoperative morbidity is classified according to the Clavien-Dindo classification. Overall, general, and surgery-related postoperative complications as well as need for readmission occurring within 30 days after surgery will be considered.Possibility to be discharged from the hospital. Ability to go back home is computed considering postoperative length of hospital stay (days).

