### Study aims and objectives

The primary aim of this study is to compare the rate of AUR after immediate compared to early (24-h) removal of UC in patients undergoing minimally invasive colonic resection (MICR). The study hypothesis is that immediate UC removal is non-inferior to 24-h UC removal in terms of AUR rate.

The secondary outcomes focus on items that could be positively impacted by the immediate removal of the UC at the end of the surgery. In particular, the rate of UTIs, perception of pain, time-to-return of bowel and physical functions, postoperative complications, and LOS will all be measured.

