### Sample size calculation

The null hypothesis is that the immediate UC removal is significantly inferior to the 24-h UC removal. Based on the current literature, in order to test the alternative hypothesis of non-inferiority of immediate UC removal vs. 24-h UC removal, the sample size is calculated using the incidence of AUR. Available data show that the AUR rate can be estimated as high as 3% after MICR [14–16].

Sample size was calculated based on the following data. Considering an expected AUR rate of 3% (p1) for the 24-h UC removal group, we choose the non-inferiority limit of δ = 6% with δ = p2-p1, considering acceptable a p2 of 9% for the immediate UC removal group. We calculated that 200 patients are required in each group to give 80% power at a 5% significance level. Considering 8% dropout, the total number of patients to be enrolled is 216, 108 per group (Non-Inferiority Tests for the Difference Between Two Proportions, PASS 14)

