### Statistical analysis

Statistical analyses will be performed on an intention-to-treat (ITT) basis using IBM® SPSS® Statistics software version 21.0 (IBM Corporation, Armonk, NY).

An intention-to-treat analysis (ITT) will be used on all randomized subjects and, where appropriate, an imputation method will be established. It will be also performed per-protocol (PP) analysis that will include all subjects who have finished the catheter removal without major deviations from the research protocol. In non-inferiority studies, both ITT and PP analyses are recommended and should support non-inferiority.

The primary endpoint is AUR. Non-inferiority in the main outcome of the immediate UC removal group compared to 24-h UC removal will be evaluated by test for proportions. The non-inferiority of the immediate UC removal group will be accepted if the upper limit of the 95% confidence interval of the difference in proportions is greater than the non-inferiority threshold value of 6%.

The secondary objectives are assessing the benefits in choosing one procedure or the other, immediate UC removal versus 24-h UC removal. Descriptive statistics and plots will be used to compare the two groups taking into account: (1) UTI rate; (2) overall rate of re-catheterization; (3) pain intensity at 6, 12, 24, 48, and 72 h after surgery; (4) time from surgery to resumption of first oral intake (liquid and soft diet), bowel movements (flatus and defecation), mobilization to chair, and walking; (5) rate of overall, general, and surgery-related post-operative complications; (6) length of hospital stay.

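### The secondary aim is worded as demonstrating non-inferiority, but the analysis section describes a descriptive look at benefit and gives no margin for any secondary outcome

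*Protocol article*

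**What the plan says.** Three places in the protocol article describe the secondary outcomes.

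- **Study aims and objectives** explains why they were chosen: "The secondary outcomes focus on items that could be positively impacted by the immediate removal of the UC at the end of the surgery". The only hypothesis stated there concerns AUR.
- **Secondary outcome measure** opens with a confirmatory aim: "To demonstrate the non-inferiority of immediate compared to 24-h removal of UC for the other short-term postoperative outcomes". It then lists seven domains: UTI, all-cause catheter reinsertion, pain to day 3, bowel function, mobilization, morbidity with readmission, and length of stay.
- **Statistical analysis** states the aim differently: "The secondary objectives are assessing the benefits in choosing one procedure or the other, immediate UC removal versus 24-h UC removal". It names the method: "Descriptive statistics and plots will be used to compare the two groups taking into account", followed by six numbered items that regroup most of the same outcomes.

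The one margin in the document belongs to the primary endpoint. Under **Sample size calculation**: "we choose the non-inferiority limit of δ = 6% with δ = p2-p1". The sample size is derived from AUR only.

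**The concern.** A non-inferiority conclusion needs a margin fixed in advance and an interval or test set against it. The Statistical analysis section supplies both for AUR and neither for any secondary outcome, and it describes the secondary question as one of benefit. A team following the outcome section would owe readers seven non-inferiority conclusions. A team following the analysis section would produce descriptive tables and plots. Both cannot be followed.

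What is at stake is how the secondary results are reported. With a non-inferiority aim on the page and no margin to judge it by, similar-looking rates, or a difference that happens not to be significant, could be written up as non-inferior. That is a risk created by the wording, not something the protocol says it will do.

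**Working it through.** **1. The stated aims side by side**

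| Section | Question for secondary outcomes | Margin | Method |
|---|---|---|---|
| Study aims and objectives | possible positive impact of immediate removal | none | will be measured |
| Secondary outcome measure | demonstrate non-inferiority | none | none |
| Statistical analysis | benefits of either procedure | none | descriptive statistics and plots |

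The first and third rows agree. The second is the outlier, so there are two conflicting aims.

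**2. The plan's own sample size, reproduced**

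Inputs from Sample size calculation: 3% AUR in the 24-h arm, margin 6 points, 80% power, 5% significance level (sidedness not stated). I assume equal true rates.

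n per arm = (z_α + z_power)² × 2p(1−p) / δ²

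One-sided 5%: (1.645 + 0.842)² × 2 × 0.03 × 0.97 / 0.06² = 100 per arm, 200 in total. Adding 8% gives 100 × 1.08 = 108 per arm, 216 in total, as printed. (The sentence putting 200 in each group fits only as a total; that is a separate matter.) No secondary outcome enters this calculation.

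**3. What 100 per arm can say about a secondary rate**

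Assumption: UTI of 4% in both arms. The Discussion gives almost 4% after colorectal surgery generally, so this is not an estimate for the trial population.

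- Standard error of the difference = √(2 × 0.04 × 0.96 / 100) = 0.0277
- 95% half-width = 1.96 × 0.0277 = 0.054, or 5.4 points, against a rate of 4%

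Smallest UTI margin that could be excluded with 80% power = (z_α + z_power) × standard error:

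- one-sided 5%: (1.645 + 0.842) × 0.0277 = 6.9 points
- one-sided 2.5%: (1.960 + 0.842) × 0.0277 = 7.8 points

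With 108 per arm these become 6.6 and 7.5 points. All exceed the assumed event rate.

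**4. What a UTI non-inferiority claim would need**

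The protocol gives no UTI margin, so a range is assumed. Same formula as step 2 with p = 0.04 and 80% power:

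| Assumed margin | n per arm, one-sided 5% | n per arm, one-sided 2.5% |
|---|---|---|
| 2 points | 1188 | 1507 |
| 4 points | 297 | 377 |
| 6 points | 132 | 168 |

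Even borrowing the 6-point AUR margin would need more than the 108 per arm to be enrolled.

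**5. Reinsertion**

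The outcome section counts AUR among the causes of all-cause reinsertion. The primary margin already tolerates up to 6 points more AUR, so non-inferior reinsertion has no defined meaning without a margin of its own.

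**The case against.** The strongest reply is that this is one loosely worded lead-in in a condensed article. The analysis section already treats the secondary outcomes descriptively, in line with the stated aims; margins and intervals may sit in an analysis plan that is not shown; and the primary endpoint, its margin and the sample size are unaffected.

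Much of this stands. The absence of secondary margins would not by itself be a finding, and the section does not rule out intervals. A descriptive comparison can also serve a descriptive look at benefit. But the conflict is in the published text: the article states a confirmatory aim and also fixes a descriptive, benefit-oriented analysis. A separate plan would have to override one of them.

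Three stronger readings are tempting, and the documents do not support them.

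- **That three different hypotheses are stated.** The aims section and the analysis section both look at possible benefit. The wording there is that outcomes could be positively affected, which is weaker than an expected benefit.
- **That accepting 6 points more AUR is justified by these benefits.** The Sample size calculation calls 9% acceptable and does not tie the margin to any secondary outcome.
- **That the trial will infer non-inferiority from non-significance.** No significance test is planned for secondary outcomes. For scale only: an observed 10/100 versus 4/100 would give z = 0.06 / √(0.07 × 0.93 × 2/100) = 1.66, two-sided p about 0.10, with an unpooled 95% interval of about −1 to +13 points. Non-significance would be a poor basis for the claim, but the protocol does not say it would be used.

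The UTI figures also have limits. The 4% comes from a broader surgical population, and the Background says the catheter raises UTI risk, so an excess with immediate removal is not the direction the protocol anticipates.

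**Conclusion.** The point holds as a contradiction within the protocol and as a stated claim that the stated analysis cannot deliver. The outcome section promises non-inferiority on seven domains; the analysis section addresses possible benefit by description; the only margin and the only sample size calculation are for AUR.

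Under an assumed 4% UTI rate in both arms and 100 per arm, the difference would be known only to within about ±5.4 points, and no UTI margin below roughly 7 points could be excluded with 80% power. These figures illustrate one outcome and rest on normal approximations and a rate from colorectal surgery generally. The contradiction itself depends on no figure.

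The primary conclusion is not affected. This should be corrected before the secondary results are written up.

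**What to change.** 1. In Secondary outcome measure, replace the lead-in with an estimation aim in line with the other two sections, for example: *to estimate the difference (immediate minus 24-h removal) in the following short-term postoperative outcomes*.
2. In Statistical analysis, report each secondary outcome as a between-group difference with a two-sided 95% confidence interval: a risk difference for rates, and a difference in means or medians for pain scores, times and length of stay. Label these analyses exploratory.
3. State that no non-inferiority claim will be made on secondary outcomes.

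The alternative is to keep the claim for a named outcome, which would need a justified margin, a confidence level and a rule for multiplicity. For UTI, the sample sizes under working show that 108 per arm would not support margins of 2 to 6 points at 80% power under the 4% assumption.

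The cost is a few sentences and an interval column in tables already planned. Recruitment, sample size and the primary analysis do not change. The downside is giving up a secondary claim that the design cannot support.

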### Sample size calculation

The null hypothesis is that the immediate UC removal is significantly inferior to the 24-h UC removal. Based on the current literature, in order to test the alternative hypothesis of non-inferiority of immediate UC removal vs. 24-h UC removal, the sample size is calculated using the incidence of AUR. Available data show that the AUR rate can be estimated as high as 3% after MICR [14–16].

Sample size was calculated based on the following data. Considering an expected AUR rate of 3% (p1) for the 24-h UC removal group, we choose the non-inferiority limit of δ = 6% with δ = p2-p1, considering acceptable a p2 of 9% for the immediate UC removal group. We calculated that 200 patients are required in each group to give 80% power at a 5% significance level. Considering 8% dropout, the total number of patients to be enrolled is 216, 108 per group (Non-Inferiority Tests for the Difference Between Two Proportions, PASS 14)

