**Methods:**

This is a prospective, randomized, controlled, two-arm, multi-center, study comparing the rate of AUR after immediate versus early removal of UC in patients undergoing MICR. The investigators hypothesize that immediate UC removal is non-inferior to 24-h UC removal in terms of AUR rate. Randomization is at the patient level and participants are randomized 1:1 to remove their UC either immediately or within 24 h from the completion of surgery. Those eligible for inclusion were patients undergoing any MICR with an anastomosis above the peritoneal reflection. Those patients who need to continue urinary output monitoring after the surgery will be excluded. The number of patients calculated to be enrolled in each group is 108 based on an expected AUR rate of 3% for the 24-h UC removal group and considering acceptable an AUR of 9% for the immediate UC removal group.

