### Allocation and sequence generation

Patients satisfying the inclusion criteria and willing to enter the study are randomized to one of the two study arms after signing the informed consent. The randomization is performed in a 1:1 fashion. The allocation to immediate or early UC removal group is achieved by creating a randomization list. The randomization list has been obtained by an online program available at https://www.sealedenvelope.com/simple-randomiser/v1/lists. A common list is created for all participating centers and patients’ allocation communicated by a member of the proposing center to a member of other centers the morning of surgery. The operating surgeon will be blinded to allocation of the patients until the end of surgery.

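### The required sample size is printed as 200 per group, but enrolment is 108 per group; the inputs point to 200 in total

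*Protocol article*

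**What the plan says.** The Sample size calculation section gives these inputs:

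- Control arm: "Considering an expected AUR rate of 3% (p1) for the 24-h UC removal group".
- Margin: "we choose the non-inferiority limit of δ = 6% with δ = p2-p1".
- Limit of acceptability in the immediate-removal arm: "considering acceptable a p2 of 9% for the immediate UC removal group".
- Requirement before dropout: "We calculated that 200 patients are required in each group to give 80% power at a 5% significance level".
- Allowance and target: "Considering 8% dropout", followed by "the total number of patients to be enrolled is 216, 108 per group".

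The Methods paragraph of the abstract repeats the target: "The number of patients calculated to be enrolled in each group is 108". Allocation is equal (Allocation and sequence generation: "The randomization is performed in a 1:1 fashion"). The section cites the PASS 14 procedure for non-inferiority of two proportions. It does not say whether the 5% level is one-sided or two-sided, what true retention rate is assumed in the immediate-removal arm, or which variance was used.

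**The concern.** The requirement before dropout (200 per group) is larger than the enrolment after dropout (108 per group). Inflating for dropout can only raise the number, so this holds whatever formula was used.

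Taken literally, the trial would enrol about half of what its own calculation demands for the primary endpoint. The literal reading cannot be dismissed at a glance. A reader who takes 3% versus 9% as the design alternative, when 9% is the control rate plus the margin, gets a figure close to 200 per group. An ethics committee, a reader of the results or a meta-analyst could then conclude that the trial is badly undersized, or could quote a requirement the trial never had.

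**Working it through.** **1. The contradiction, without any model**

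If 200 per group were required:

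- Multiplying by 1.08: 200 x 1.08 = 216 per group, 432 in total.
- Dividing by 1 - 0.08: 200 / 0.92 = 217.4, so 218 per group, 436 in total.

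The article plans 108 per group. The ratios are 200/108 = 1.85 as printed, and 216/108 = 2.00 or 218/108 = 2.02 once dropout is included.

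**2. Which figure do the inputs support?**

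From the article: control rate 0.03, margin 0.06, power 80% (z = 0.842), 1:1 allocation. Assumed here: true rate 0.03 in both arms, one-sided 5% (z = 1.645), unpooled variance.

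n per group = (z_alpha + z_beta)^2 x 2 x p(1 - p) / margin^2
= (1.645 + 0.842)^2 x 2 x 0.03 x 0.97 / 0.06^2
= 99.95, so **100 per group, 200 in total**.

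Dropout: 200 x 1.08 = 216 and 100 x 1.08 = 108, which are both printed targets exactly. Dividing by 0.92 instead gives 109 per group, 218 in total. Conversely, 216 x 0.92 = 198.7, or about 199 evaluable patients.

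**3. Power under each reading**

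Power = Phi(0.06 / sqrt(2 x 0.0291 / n) - z_alpha), where 0.0291 = 0.03 x 0.97.

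| n per group | One-sided 5% | One-sided 2.5% |
|---|---|---|
| 100 | 80.0% | 70.1% |
| 200 | 96.9% | 94.0% |

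On this formula the stated 80% belongs to 100 per group at one-sided 5%. It does not belong to 200 per group at either level.

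**4. Could another method give 200 per group?**

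All values are per group, for 80% power, before dropout. The continuity-corrected size is (n/4) x (1 + sqrt(1 + 4/(0.06 n)))^2. The Farrington-Manning size uses constrained rates of 1.81% and 7.81% for the null variance.

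| Method | One-sided 5% | One-sided 2.5% |
|---|---|---|
| Unpooled | 100 | 127 |
| Unpooled, continuity correction | 132 | 159 |
| Farrington-Manning | 135 | 174 |
| Farrington-Manning, continuity correction | 167 | 206 |

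A superiority comparison of 3% with 9% would need 193 per group (one-sided 5%) or 245 (two-sided 5%). The values nearest 200 are therefore 193, which answers a different question, and 206, from an unusual variant at one-sided 2.5%. Neither can lead to 108 per group after a dropout allowance. Only the first cell reproduces the whole printed sequence: 200 in total, then 216, then 108 per group.

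**The case against.** The strongest reply is that this is a slip of wording. The enrolment target is the same wherever it appears, and 200 x 1.08 = 216 makes it nearly certain that the 200 was meant as a total. On that reading the trial is not half-sized: about 199 evaluable patients against 200 needed is essentially no shortfall. Nothing in the enrolment, margin or analysis changes because of the misprint. This stands, and the factor of two should not be read as under-recruitment.

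It can also be said that 100 per group depends on assumptions the article does not state, since other methods give 127 to 206. That stands too: 100 per group is an inference, though the only one tried that reproduces every printed figure, and it needs confirming against the software output. The contradiction itself needs no such assumption.

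Lastly, printing 100 per group for 80% power may leave a power claim that does not match the analysis. The Statistical analysis section judges non-inferiority on the upper limit of a 95% confidence interval. If that interval is two-sided, the level is one-sided 2.5%, 100 evaluable per group gives about 70% power, and 127 would be needed. This is a separate matter from the misprint, but it is a reason to state the sidedness when the sentence is corrected.

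The reply does not make the correction optional. The required sample size for the primary endpoint is a figure others rely on, it is wrong as printed, and nothing else in the article repairs it.

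**Conclusion.** The concern holds. The stated requirement and the stated enrolment cannot both be right; they differ by a factor of 1.85 as printed and about 2 after dropout. That conclusion rests on no assumption.

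The per-group label on the 200 is almost certainly the error. The figure that reproduces the article's targets is 100 evaluable per group, 200 in total. This rests on a true retention rate of 3% in both arms, a one-sided 5% level, unpooled variance, and dropout applied by multiplying by 1.08. On that reading the enrolment of 216 agrees with the trial's own calculation. It must be fixed because a headline figure for the primary endpoint is misstated; the misprint by itself does not show a shortage of patients.

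**What to change.** 1. Check the original PASS output. If it confirms the inference, change the sentence to say that 100 evaluable patients per group (200 in total) are required. If it shows something else, the enrolment target must be reconciled with it.
2. In the same place, state what reproduces the number: a true retention rate of 3% in both arms, a margin of 6 percentage points, the test and variance used, and the one-sided level. Make clear that 9% is the control rate plus the margin and not the rate assumed for the power calculation.
3. State the power that goes with the level implied by the 95% confidence interval rule, so that the corrected sentence does not carry an 80% claim the analysis does not support.

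The correction costs a sentence or two and no additional patients. Any question of adding patients would come from item 3, not from this misprint.

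### The stated 80% power belongs to a one-sided 5% test; under the 95% confidence interval that decides the trial, power is about 70%

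*Protocol article*

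**What the plan says.** The design inputs are in the protocol article, Sample size calculation. The control rate is given as "Considering an expected AUR rate of 3% (p1) for the 24-h UC removal group", and the margin as "we choose the non-inferiority limit of δ = 6% with δ = p2-p1, considering acceptable a p2 of 9" per cent. The error rates are given as "to give 80% power at a 5% significance level", with no sidedness. The section then prints "We calculated that 200 patients are required in each group", followed by "Considering 8% dropout, the total number of patients to be enrolled is 216, 108 per group". The abstract (Methods) agrees with the last figure: "The number of patients calculated to be enrolled in each group is 108".

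The decision rule is in the Statistical analysis section. It compares "the upper limit of the 95% confidence interval of the difference in proportions" with the 6% threshold and does not describe the interval as one-sided.

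**The concern.** A non-inferiority decision uses one end of the interval. The upper limit of a conventional 95% interval leaves 2.5% in the upper tail, so the rule is a one-sided test at 2.5%. If the 5% in the sample size section was one-sided, it corresponds to a 90% two-sided interval, and the trial was sized for an easier test than the one it will apply.

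At stake is the main design claim. With too little power, immediate removal could be truly no worse and still fail the test more often than the protocol tells its readers. A second, smaller matter is that two error rates in one document leave a foothold for arguing for a 90% interval once results are known.

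**Working it through.** **Inputs**
- Control rate 3%, margin 6 points, power 80%, alpha 5% (sidedness not given), dropout 8%, 216 enrolled, 108 per group: Sample size calculation.
- Two-sided 95% interval, hence one-sided 2.5%: Statistical analysis, on the usual meaning of the term.
- True rate in the immediate-removal arm: not stated. Assumed to be 3%, so no true difference. The 9% is the largest acceptable rate, not the expected one.
- Evaluable number: printed as 200 per group. That cannot come from 216 enrolled in total, so it is read as 200 in total, 100 per group.

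**Step 1. Reproduce the plan's number.** With unpooled variance,

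n per group = (z(1−α) + z(power))² × [p1(1−p1) + p2(1−p2)] / margin²

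The variance term is 2 × 0.03 × 0.97 = 0.0582, and margin² = 0.0036.

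- One-sided 5%: (1.645 + 0.842)² × 0.0582 / 0.0036 = 99.95, so 100 per group and 200 in total. Then 100 × 1.08 = 108 per group and 216 in total. This matches the plan exactly.
- One-sided 2.5%: (1.960 + 0.842)² × 0.0582 / 0.0036 = 126.9, so 127 per group. This does not match.

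Other variants at one-sided 5% also miss 100 per group: Farrington-Manning gives 135, null variance at 3% and 9% gives 157, and a continuity correction gives 132. Of the calculations tried, only the unpooled formula at one-sided 5% yields the plan's number.

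**Step 2. Power under the rule to be applied.** Power = Φ(margin / SE − z(1−α)), with SE = √(0.0582 / n).

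| Evaluable per group | One-sided 5% | One-sided 2.5% (95% CI) |
|---|---|---|
| 99 (108 less 8%) | 79.7% | 69.7% |
| 100 | 80.0% | 70.1% |
| 108 (no dropout) | 82.6% | 73.4% |

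For n = 100: SE = √(0.0582 / 100) = 0.02412 and 0.06 / 0.02412 = 2.487. So Φ(2.487 − 1.645) = 0.800 and Φ(2.487 − 1.960) = 0.701.

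**Step 3. Check by exact enumeration.** Summing binomial probabilities over all outcomes that satisfy the Wald 95% rule gives 70.6% at 100 per group and 73.8% at 108. With Newcombe or Farrington-Manning 95% limits, exact power is about 55% at 100 and 59% at 108. About 70% is therefore the favourable end across interval methods.

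**Step 4. Can the choice of interval change the conclusion?** Take 100 per group and the Wald interval.
- 3 events (24-h) and 4 events (immediate): difference 1.0 point, SE = √[(0.03 × 0.97 + 0.04 × 0.96) / 100] = 0.0260. The upper limit is 5.3% on a 90% interval and 6.1% on a 95% interval.
- 5 events in each group: difference 0, SE = √[2 × 0.05 × 0.95 / 100] = 0.0308. The upper limit is 5.1% on a 90% interval and 6.04% on a 95% interval.

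Both results pass on the 90% interval and fail on the 95% interval, and both lie close to the event counts the protocol expects.

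**The case against.** **Sidedness is nowhere stated.** Only the upper limit is used, so a one-sided 95% limit may have been meant. In that case design and analysis would agree at 80%. This is the best argument, and it shows that the shortfall depends on the conventional reading. But nothing in the Statistical analysis section calls the interval one-sided, and an unqualified 95% confidence interval is ordinarily two-sided. Even if a one-sided limit was intended, the text must say so.

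**The printed number is 200 per group.** At that size, power against the two-sided 95% limit would be about 94%. It cannot stand beside 216 enrolled and 108 per group, so it does not rescue the power. It is a separate misprint to correct.

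**70% is one point in a range.** This is fair. An intention-to-treat analysis of all 108 per group would have 73.4%, although the Withdrawal section removes patients who withdraw. The protocol presents 3% as an upper-end estimate. At a true 2% in both arms, power at one-sided 2.5% would be 86% (n = 100) or 88% (n = 108). But 2% is not the design assumption, and the gap between the two alphas remains: at n = 100, Φ(3.031 − 1.645) is about 92% against 86%. In the other direction, a true excess in the immediate arm lowers power sharply.

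**The error is conservative.** On the conventional reading, the rule applied is the stricter one, so the mismatch does not by itself raise the risk of a false non-inferiority claim. That is correct. The harm is an inconclusive trial and an overstated power. A later move to a 90% interval would also be a visible departure from the published rule, so that risk is secondary.

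**Conclusion.** The point holds. The sample size was computed at one-sided 5%, while the stated decision rule is, on its ordinary meaning, one-sided 2.5%. Power under that rule is about 70% with 100 evaluable per group, and at most about 73% with all 108, against the stated 80%. The type II error is about 30% rather than 20%. No dropout rate within the planned 216 restores 80% at the design rate of 3%.

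This rests on three readings: the 95% interval is two-sided; 200 is the total evaluable number; and the true rate is 3% in both arms, which is unstated but is the assumption that reproduces the plan's number. The last one is favourable with respect to the true difference. As an illustration only, take the 6.8% (removal at end of surgery) and 4.2% (within 24 h) of the retrospective cohort described in the Background. Power at 100 per group is then Φ((0.06 − 0.026) / 0.0322 − 1.960), about 18%, or about 28% at one-sided 5%. That cohort mixed open and minimally invasive colorectal surgery, its groups did not differ significantly, and the conclusion here does not depend on it.

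**What to change.** Keep the two-sided 95% interval as the decision rule, and name the alpha as one-sided 2.5% in both Sample size calculation and Statistical analysis. Replace the power statement with wording such as: With 100 evaluable patients per group and a true retention rate of 3% in both arms, power to show non-inferiority at a 6-point margin is about 70% at one-sided 2.5% (about 73% if all 108 per group are evaluable). Beside it, give the power for a small true difference, and state that the base case assumes none.

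This costs wording only. No patients are added, and the reported power becomes less favourable. If the sponsor wants to keep 80%, 127 evaluable per group (254 in total) are needed. That means 138 enrolled per group (276) with the protocol's multiplication by 1.08, or 139 per group (278) when dividing by 0.92. If a one-sided 5% test was intended from the start, the protocol should say so, justify it, and specify the matching 90% two-sided interval before any results are seen.

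Two nearby errors should be corrected in the same edit. One is the figure of 200 per group. The other is the acceptance rule in Statistical analysis, which as printed accepts non-inferiority when the upper limit lies above 6% instead of below it.
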